The study is build up in three phases:

In the first phase, 95 patient data are included, in phase 2 and 3 92 (total 279). This number of cases is taken from the biometric report. The city of Osnabrück and the district of Osnabrück have a combined population of 506,000 (as of Dec. 2013) (17). Every year about 300-400 out-of-hospital resuscitation attempts can be expected.

- **Phase 1:** Data is recorded without using the accelerometer (real-time feedback system). The analysis of chest compression frequency and interruptions is done via ECG evaluation. The data of the resuscitation register will be used to analyze the clinical data.
- **Phase 2:** Data is recorded using the feedback sensor without giving a real-time feedback to the Emergency medical staff. The analysis of chest compression frequency and interruptions is done via ECG evaluation. The data of the resuscitation register will be used to analyze the clinical data.
- **Phase 3**: Data is recorded using the feedback sensor and the Emergency medical staff receives a real-time feedback on chest compression quality. The analysis of chest compression frequency and interruptions is done via ECG evaluation. The data of the resuscitation register will be used to analyze the clinical data.

Data flow of the device data:

1. The patient data of each resuscitation are loaded via mobile data transfer to a server and is retrieved from there for evaluation. This corresponds to the usual procedure in the rescue services. The resuscitation missions are subsequently identified in the collective of missions.

2. The data for the resuscitation quality are loaded via mobile data transfer to a server and from there after identification of the inserts (see point 1) for evaluation. The data records are sent anonymously to the corpuls company:
[figure not shown]

The anonymization will be done via filters. The individual data are listed below. Any data that could lead to patient identification, directly or in combination with other data, will be removed. The contents are no longer available in the evaluation database and can no longer be retrofitted.

| Patientendaten | | | | |
| --- | --- | --- | --- | --- |

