| **Dauer des Einsatzes (Einsatzende)** | [figure not shown] | [figure not shown] | identifizierende Daten entfernen, damit sind auch diese Daten kein PHI mehr | [figure not shown] |
| **Seriennummer der einzelnen Gerätemodule** | [figure not shown] |  | Daten werden entfernt. | [figure not shown] |
| **Seriennummer der einzelnen Geräteoptionen** | [figure not shown] |  | Daten werden entfernt. | [figure not shown] |
| **Kontinuierlich aufgezeichnete Kurven** | [figure not shown] | [figure not shown] | identifizierende Daten entfernen, damit sind auch diese Daten kein PHI mehr | [figure not shown] |
| **Kontinuierlich aufgezeichnete Vitalparameter** | [figure not shown] | [figure not shown] | identifizierende Daten entfernen, damit sind auch diese Daten kein PHI mehr | [figure not shown] |
| **12-Kanal-EKG** | [figure not shown] | [figure not shown] | identifizierende Daten entfernen, damit sind auch diese Daten kein PHI mehr | [figure not shown] |
| **12-Kanal-EKG Vermessung, Diagnose und Therapieempfehlung (HES)** | [figure not shown] | [figure not shown] | identifizierende Daten entfernen, damit sind auch diese Daten kein PHI mehr | [figure not shown] |

Data flow of patient data:

The mission is documented in the German Resuscitation Register and retrieved from there for evaluation. In the resuscitation register, the mission is pseudonymised stored under a mission number and can be retrieved from there for evaluation on the application number, without the data that allows a direct identification of the patient can be accessed.

Matching patient and device data:

The matching takes place on a computer of the University Hospital Münster as shown.

Statistics:

The statistical calculations were based on the knowledge from the study Kramer Johansen et al. "Quality of out-of-hospital cardiopulmonary resuscitation with real-time automated feedback: a prospective interventional study".

1. Endpoint 1.1: Phase 1 data are used as a reference for chest compression frequency and pauses in compression; Phase 2 data is used as a reference for the depth of compression. These phases are compared with the subsequent phases relating to quality.
2. Endpoint 1.2: The data is assessed phase-specifically for the percentage deviation from the ERC Reanimation Guidelines recommendations.
3. It is analysed whether phase-specific differences in short-term survival are recognizable.

Kompressionsfrequenz

Unterbrechung der Kompression

Kompressionstiefe

Phase 2

Phase 1

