Phase 3

Phase 2

Phase 3

The multiple significance levels are set at 5%, and the power should always be ≥ 80% (error 2nd type ≤ 20%).

There are one or more comparisons for each target size. The multiple significance level of 5% is divided into Bonferronie targets in three parts (weighted):

1. For the comparisons concerning the depth of the compression, a local significance level of 1/4 * 5% is used. Here only the groups Phase 2 and Phase 3 are compared with each other with respect to the Mann-Whitney-U-test for the local significance level 1/4 * 5%.
2. For the comparisons regarding the compression frequency, a local significance level of 1/4 * 5% is used. Here the groups Phase1, Phase 2 and Phase 3 are compared with each other in pairs to the local significance level 1/4 * 5%. This results in 3 group comparisons. The multiple test problem is solved here by using the final test (for the pair comparisons the Mann-Whitney U test is used, for the 3 group comparisons (cutting hypothesis) the Kruskal-Wallis test is used).
3. For the comparisons concerning pauses in compression, a local significance level of 1/2 * 5% is used. Here, the groups Phase1, Phase 2 and Phase 3 are compared with each other in pairs to the local significance level 1/2 * 5%. This results in 3 group comparisons. The multiple test problem is solved here by using the final test (for the pair comparisons the Mann-Whitney U test is used, for the 3 group comparisons (cutting hypothesis) the Kruskal-Wallis test is used).

Powercalculation and number of cases:

The Phase 1 treatment group requires 95 patients, the Phase 2 treatment group requires 92 patients, and the Phase 3 treatment group requires 92 patients. In total, 95 + 92 + 92 = 279 patients are needed for this project.

1. For the comparisons of compression depth, with these numbers of patients a power of 82.1% is achieved.
2. For the comparisons of compression frequency, a power of 86.5% is achieved with these patient numbers (= probability that all three pair comparisons will yield a significant result).
3. For the comparisons of pauses in compression, with these patient numbers a power of 80.1% is achieved (= probability that all three pair comparisons yield a significant result).

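### Sequential, non-randomised phases are compared without adjustment although registry data are matched to each case, so case mix or calendar time can be read as a feedback effect

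*Supplement*

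**What the plan says.** **Design.** The Design section states: "The study is build up in three phases". Phase 1 has no sensor. Phase 2 has the sensor but no feedback: "Data is recorded using the feedback sensor without giving a real-time feedback to the Emergency medical staff". Phase 3 has the sensor with feedback. No randomisation, concurrent control or crossover is described. The order in time follows from the Statistics section: "These phases are compared with the subsequent phases relating to quality".

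**Analysis.** Depth is compared between Phases 2 and 3 by Mann-Whitney at a local level of 1.25%. Frequency (1.25%) and pauses (2.5%) are compared over all three pairs by Mann-Whitney, with a Kruskal-Wallis test for the three-group hypothesis. I read this as a closed test. Hodges-Lehmann estimates with 95% confidence intervals and an exploratory split by gender are added. There is no covariate, regression model, date term, comparison of case mix between phases or sensitivity analysis. For survival the plan is one sentence: "It is analysed whether phase-specific differences in short-term survival are recognizable".

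**Available data.** For every phase the Design section says: "The data of the resuscitation register will be used to analyze the clinical data". A later paragraph provides for matching patient data with device data.

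**Size and caseload.** "In total, 95 + 92 + 92 = 279 patients are needed for this project". "Every year about 300-400 out-of-hospital resuscitation attempts can be expected".

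**The concern.** The stated hypothesis is causal: the feedback system changes resuscitation quality compared with conventional resuscitation. Phase is the only carrier of the intervention, and phase is tied to calendar time. Anything else that differs between phases enters the phase contrast in full, for example patient mix, season, or crews becoming used to the sensor or to being measured. A rank test on phase alone cannot separate these from feedback.

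The plan's own power statement shows the difficulty. For frequency and pauses, power is the probability that all three pairs are significant. That includes Phase 1 vs 2, where neither phase gives feedback. The plan is therefore powered to find a shift without feedback, but has no analysis to explain one.

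At stake are the attribution of the main quality result and the reading of the ROSC comparison, for which case mix is an obvious competing explanation.

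**Working it through.** **1. The plan's own figures.** Alpha: 1.25% + 1.25% + 2.5% = 5%. Sample: 95 + 92 + 92 = 279. Both agree. The stated powers cannot be reproduced because no effect size or SD is given. Inverting the 82.1% for depth, two-sided (sidedness is not stated), gives (2.498 + 0.919) × √(2/92) = 0.504 SD. With rank-test efficiency as low as 0.864 it is 0.542 SD. The planned effect is thus about 0.50 to 0.54 SD.

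**2. Phase length.** Months = n / annual attempts × 12.
- Shortest phase: 92/400 × 12 = 2.8. Longest: 95/300 × 12 = 3.8.
- Whole study: 279/400 × 12 = 8.4 to 279/300 × 12 = 11.2.
- These are minima, since they assume that every attempt is included. At an assumed 50% inclusion a phase lasts 92/200 × 12 = 5.5 to 95/150 × 12 = 7.6 months.

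**3. Depth, Phase 2 vs 3, no feedback effect.** Let δ be the drift per phase in SD (an assumption). With Mann-Whitney efficiency 3/π, s = δ × √(3/π) / √(1/92 + 1/92). The critical value at 1.25% two-sided is c = 2.498, and P(reject) = Φ(s − c) + Φ(−s − c).

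| δ | s | P(reject), nominal 1.25% |
|---|---|---|
| 0.05 | 0.331 | 1.7% |
| 0.10 | 0.663 | 3.4% |
| 0.15 | 0.994 | 6.7% |
| 0.20 | 1.326 | 12% |

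**4. Phase 1 vs 3, frequency and pauses, no feedback effect.** At δ = 0.15 the two phases differ by 0.30 SD and s = 2.004. The pairwise test alone would reject about 31% (c = 2.498) or 41% (c = 2.241) of the time. The plan also requires the Kruskal-Wallis test to reject. Simulating that closed test (normal outcomes, 95/92/92, 6,000 runs) gives about 20% at 1.25% and 29% at 2.5%. Repeat runs vary by about one percentage point.

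**5. What adjustment can remove.** Simulation with 92 vs 92, level 1.25%, no feedback effect and 4,000 runs. A measured case-mix variable, correlated 0.5 or 0.7 with the outcome, shifts between phases (all assumed). Linear regression stands in for the adjusted model.

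| Shift | Correlation | Mann-Whitney | Adjusted |
|---|---|---|---|
| 0.3 SD | 0.5 | 6.9% | 1.2% |
| 0.3 SD | 0.7 | 12.7% | 1.5% |
| 0.5 SD | 0.5 | 20.3% | 1.2% |
| 0.5 SD | 0.7 | 39.5% | 1.1% |

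**6. What a date term costs.** With 279 evenly spaced cases, adding a linear date term multiplies the standard error by 1.71 for Phase 3 vs 2 and by 3.00 for Phase 3 vs 1. For depth, the 82.1% power would become Φ(3.417/1.71 − 2.498) = Φ(−0.50) ≈ 31%.

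**The case against.** Five points can be made for the plan.

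- **The error rates are valid for what is tested.** A reader might infer that the 1.25% and 2.5% levels fail if anything drifts. They do not. The null is no difference between phases, and the Indicators section defines the endpoint as a change relative to Phase 1. This stands: attribution is exposed, not error control.
- **The closed test dampens false signals.** A reader might take the pairwise 31% and 41% as the plan's rates. They ignore the Kruskal-Wallis step. This stands, and about 20% and 29% are the relevant figures.
- **Phase 2 is a safeguard.** Phase 1 vs 2 compares two phases without feedback and so gives a partial drift check. This stands for frequency and pauses, but the check is mixed with any effect of the sensor. Depth has no such check, because only Phases 2 and 3 are compared.
- **Timing is inferred.** No phase dates are given and eligibility removes some attempts. The documents support a minimum phase length, not that each phase occupies a particular season.
- **Models are often left to a separate analysis plan, and the biometric report is not shown.** This has some force for the secondary endpoint. It has less for the primary ones, because the protocol sets out their tests and levels in detail without adjustment. The registry variables are not listed, and age and sex are stripped from the device records, so covariate availability must be confirmed. The planned gender split does imply that sex will be at hand.

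**Conclusion.** The point holds as a gap between a causal hypothesis and an unadjusted comparison of sequential phases. Under an assumed drift of 0.05 to 0.2 SD per phase and no feedback effect, the depth comparison is significant about 1.7% to 12% of the time against 1.25%. At 0.15 SD, Phase 1 vs 3 is significant about 20% (against 1.25%) or 29% (against 2.5%). The drift values are illustrative. The documents contain no evidence that drift of this size occurs, so a reader should not conclude that the result will be biased, only that the planned analysis could not tell.

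Nor should a reader infer that registry adjustment would make the comparison causal. It can remove measured case mix. It cannot remove season or crew learning, because phase and date are nearly collinear. This should be corrected, since the change is cheap and bears on the main conclusion, but it does not invalidate the planned tests.

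**What to change.** 1. Keep the rank tests and the alpha split as the confirmatory tests of a phase difference.
2. Pre-specify supportive adjusted analyses: proportional-odds regression for depth, frequency and pauses, and logistic regression for admission with ROSC. Include phase plus registry variables fixed before crew action: age and sex, and first rhythm, witnessed status and location where recorded. List these after checking that the registry holds them.
3. Report case mix and calendar dates by phase. Add a linear date term as a sensitivity analysis only, labelled as low precision (standard error × 1.7 for Phase 3 vs 2, × 3.0 for Phase 3 vs 1).
4. Write down the attribution rule. A difference is ascribed to feedback only if the adjusted Phase 3 vs 2 estimate has the same direction and its confidence interval excludes no effect. State the interval's level in advance; the plan already uses 95% for its estimates. Otherwise report an association with phase. In either case state that season and learning cannot be fully excluded.

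**Cost.** Some extra analysis work and a more cautious conclusion. Sample size and alpha do not change, and no new data are needed if the registry holds the covariates.

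### The 5% level is split in fixed shares across depth, frequency and pauses; a weighted Holm step with the same weights would never lose power and could gain some at the same familywise level

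*Supplement*

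**What the plan says.** The Statistics section sets the overall requirement: "The multiple significance levels are set at 5%, and the power should always be ≥ 80% (error 2nd type ≤ 20"%). It then divides the level: "The multiple significance level of 5% is divided into Bonferronie targets in three parts (weighted"). The three shares are:

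- Depth: "For the comparisons concerning the depth of the compression, a local significance level of 1/4 * 5% is used". There is one comparison, Phase 2 against Phase 3.
- Frequency: "For the comparisons regarding the compression frequency, a local significance level of 1/4 * 5% is used". There are three pairwise comparisons.
- Pauses: "For the comparisons concerning pauses in compression, a local significance level of 1/2 * 5% is used". There are again three pairwise comparisons.

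Inside frequency and inside pauses the plan says: "The multiple test problem is solved here by using the final test (for the pair comparisons the Mann-Whitney U test is used", with Kruskal-Wallis for the three-group hypothesis. I read this as a closed test, in which a pair is declared different only if the global test and its own pair test are both significant at the local level.

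Under Powercalculation and number of cases the powers are 82.1% for depth ("with these numbers of patients a power of 82.1% is achieved"), 86.5% for frequency and 80.1% for pauses. The last two are defined as the chance that all three pairs are significant. On numbers: "In total, 95 + 92 + 92 = 279 patients are needed for this project".

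Nothing in the Statistics section says what happens to a target's share once that target has been rejected.

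**The concern.** The plan uses the closure principle within frequency and within pauses but stops at the boundary between targets. There each target keeps its starting share whatever the other two show. Weighted Holm is the closed form of the same weighted Bonferroni split, so the fixed split is dominated: it can never reject more and will sometimes reject less.

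What is at stake is power. Pauses are planned at 80.1% against a requirement of 80%, a margin of 0.1 point. A smaller effect or fewer usable recordings than planned would take that target below the plan's own requirement, and alpha passed on from another target would offset part of the loss.

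**Working it through.** **1. The plan's own arithmetic.** 1.25% + 1.25% + 2.5% = 5.00%, and 95 + 92 + 92 = 279. Both are exact. The powers cannot be reproduced independently, because the protocol names a source study but gives no effect sizes or standard deviations. I therefore take the stated powers as inputs and solve back for effects that match them.

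**2. Levels under weighted Holm.** A remaining target is tested at 5% × (its weight) / (sum of remaining weights).

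| Already rejected | Depth | Frequency | Pauses |
|---|---|---|---|
| none | 1.25% | 1.25% | 2.5% |
| depth | – | 1.67% | 3.33% |
| frequency | 1.67% | – | 3.33% |
| pauses | 2.5% | 2.5% | – |
| the other two | 5% | 5% | 5% |

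No level is below the planned one, so every rejection under the fixed split is kept.

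**3. Error control.** A target releases its share only after all its hypotheses are rejected. A target that contains a true null hypothesis therefore cannot release alpha before a false rejection has already occurred. Until then, the levels of the targets that contain true nulls sum to at most 5%. Simulation (1,000,000 runs, five null configurations) gave a familywise error of 4.9-5.0%.

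**4. Depth by hand.** Assume two-sided tests (sidedness is not stated) and a normal approximation. With 92 against 92, power ≈ Φ(d/√(2/92) − z). Setting this to 82.1% at 1.25% (z = 2.498) gives d = 0.504 and d/√(2/92) = 3.417. Then:

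- 1.25%: 82.1%
- 1.67% (z = 2.394): 84.7%
- 2.5% (z = 2.241): 88.0%
- 5% (z = 1.960): 92.7%

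If the targets are independent, a lower bound on depth power under Holm weights these by what frequency and pauses achieve at their starting levels:

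- both rejected: 0.865 × 0.801 × 0.927 = 0.643
- pauses only: 0.135 × 0.801 × 0.880 = 0.095
- frequency only: 0.865 × 0.199 × 0.847 = 0.146
- neither: 0.135 × 0.199 × 0.821 = 0.022

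The sum is about 90.6%. It leaves out cases where frequency and pauses first help each other.

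**5. All three targets by simulation.** The inputs are the stated powers, 95/92/92 patients, and the requirement that the global test and all three pairs be significant. Phase spacing and between-target correlation are assumed.

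| Phase spacing | Correlation | Depth | Frequency | Pauses | All three: fixed → Holm |
|---|---|---|---|---|---|
| equal | 0 | 91.0% | 94.3% | 87.2% | 57% → 78% |
| equal | 0.3 | 90.7% | 93.6% | 86.8% | 59% → 79% |
| equal | 0.6 | 90.2% | 92.5% | 86.3% | 63% → 80% |
| 0 : 0.8 : 2 | 0 | 90.9% | 93.5% | 86.1% | 57% → 76% |
| 0 : 0.8 : 2 | 0.3 | 91.3% | 92.9% | 86.0% | 57% → 76% |
| 0 : 0.8 : 2 | 0.6 | 91.8% | 92.0% | 85.8% | 59% → 77% |

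The 57% under independence is 0.821 × 0.865 × 0.801 = 0.569. A simpler model, with each target as one normal test statistic matched to its stated power, gave 90.9%, 93.5% and 86.0% at correlation 0, and 89.1%, 91.5% and 85.1% at correlation 0.5.

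**6. If Phase 1 and Phase 2 do not differ.** Assume equal Phase 1 and Phase 2 means for frequency and pauses, Phase 3 shifted by 0.45 to 0.55 SD, and independent targets. Those two families then rarely reject all three pairs and rarely release alpha. Depth power rises by about 0.1 point at most. Power for Phase 2 against Phase 3 rises by about 1.7-3.1 points for frequency and 1.3-2.8 points for pauses, almost all of it from alpha released by depth.

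**The case against.** The strongest reply is that nothing is broken. Weighted Bonferroni is a valid method, the shares sum to 5%, and all three stated powers reach 80%. A power of 80.1% is what a design sized to its own criterion looks like. This stands. A reader might infer that the trial is underpowered or that the familywise level is not held, and the protocol supports neither inference.

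The size of the gain is also conditional. Under Design, Phases 1 and 2 differ only in a sensor that records without giving feedback, so a Phase 1 against Phase 2 difference is not assured. A reader might take 91% for depth as what Holm delivers. That holds only if the plan's all-three-pairs powers hold, and step 6 shows what happens otherwise. A reader might also take the figures in step 5 as upper bounds, because a family passes alpha on only when all its pairs are rejected. That does not follow: the stated 86.5% and 80.1% already require all three pairs, so the condition is in the inputs.

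A fixed split also lets each target be judged without regard to the others and allows simple simultaneous intervals. The plan does not use the second advantage, since it calls for 95% intervals and not intervals at the local levels (98.75% and 97.5%).

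Finally, the section on pauses in compression lists several measures, and the Statistics section does not say which one is tested. Full rejection of the pauses family must be defined before its share can move. Endpoint 1.2, also primary, lies outside the split, so the statements on error control here cover only the three targets.

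**Conclusion.** The point holds as an optional improvement of low importance. The dominance of weighted Holm over the fixed split does not depend on effect size or correlation; only the size of the gain does. If the stated powers hold, with correlations of 0 to 0.6 and the assumed phase patterns, the gain is about 7-10 points for depth, 5-8 for frequency and 5-7 for pauses, and roughly 17-21 points for success on all three. Without a Phase 1 against Phase 2 difference, it shrinks to almost nothing for depth and to about 1-3 points for Phase 2 against Phase 3 in the other two targets. All power figures rest on back-solved effects, two-sided tests and a normal approximation to the rank tests.

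**What to change.** Add to the Statistics section that the three targets are tested by weighted Holm with weights 1/4, 1/4 and 1/2. Once depth is rejected, or all three pair hypotheses of the frequency or pauses family are rejected, that target's alpha goes to the remaining targets in proportion to their weights. State that the Kruskal-Wallis/Mann-Whitney closed test inside each family is run at the updated level. In the same place, name the pause measure that is tested, so that rejection of that family is unambiguous.

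The cost is a few sentences, to be fixed before the data are analysed. The tests, the sample size and the 5% level stay as they are. The only thing given up is the option of simple simultaneous intervals matched to the fixed shares, which the plan does not use.

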**OSCAR – OSNABRÜCK STUDY ON CARDIAC ARREST**

**Study protocol**

Introduction

In particular, the quality of chest compression quality during resuscitation was identified as an influencing factor for survival of cardiac arrest (1,2,3,4). Pre-hospital as well as in-hospital studies with professional medical staff show sobering quality results. Thorax compression depth and frequency did often not meet the guidelines (2.4) and chest compression was frequently discontinued resulting in blood flow arrest (5). Even emergency medical personnel trained on the guidelines were unable to comply with the required recommendations for resuscitation quality in resuscitation scenario (2,4,5). In a study from Norway, no rescue team reached the required guidelines recommendations on resuscitation quality (6). Both from safety-relevant fields of work such as power plants or aviation (7), as well as from acute medical work areas is known that stress can lead to a limitation of perception. Von Rittenberger were able to show this for behavior in cardiac arrest situations. With increasing complexity, the performance of Emergency medical staff deteriorated in simulated resuscitation scenarios (8).

In order to optimize the chest compression quality, the industry has developed in recent years measuring instruments that can measure the chest compression depth and frequency as well as the interruption of compression during resuscitation. If deviations from the standard occur when using these devices, audiovisual feedback is given to the staff. In addition, these devices record data from the entire course of the resuscitation and thus allow an evaluation. These devices have been named real-time feedback system (RTF)(9). The aim of using real-time feedback systems is to comply with the guidelines for chest compression depth and frequency and to minimize interruptions in compression. The current reanimation guidelines published in 2010 emphasize the importance of ensuring "high-quality resuscitation" as one of the most important predictors of patient survival (10,11). The guidelines provide a chest compression depth of 5 - 6 cm for adult resuscitation, followed by total chest relief.

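### Reaching the guideline windows for depth and frequency is a primary endpoint, but all alpha goes to non-directional comparisons that can miss movement into the window

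*Supplement*

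**What the plan says.** The Introduction states the purpose: "The aim of using real-time feedback systems is to comply with the guidelines for chest compression depth and frequency". It gives both targets as windows, 5-6 cm and 100-120/min. Under Endpoint, there are two primary parts: 1.1, a change in quality, and 1.2, reaching the guideline targets. The Indicators section asks of 1.1 only a significant change, without direction. For 1.2 it asks for the percentage deviation from 5.0-6.0 cm and, for frequency, from the single value 100/min.

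Under Statistics, the 5% is split in three:
- Depth: "Here only the groups Phase 2 and Phase 3 are compared with each other with respect to the Mann-Whitney-U-test for the local significance level 1/4" of 5%.
- Frequency: "Here the groups Phase1, Phase 2 and Phase 3 are compared with each other in pairs to the local significance level 1/4 * 5"%, closed with a Kruskal-Wallis test.
- Pauses: "For the comparisons concerning pauses in compression, a local significance level of 1/2 * 5% is used".

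The stated powers (82.1%, 86.5%, 80.1%) belong to these comparisons. For Endpoint 1.2 the Statistics section says only: "The data is assessed phase-specifically for the percentage deviation from the ERC Reanimation Guidelines recommendations". No test, alpha share or power is named for it. Hodges-Lehmann estimates with 95% confidence intervals are planned for the group differences.

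**The concern.** A window can be missed on either side. Feedback asks slow crews to speed up and fast crews to slow down, so part of its effect may be less spread around a centre that hardly moves. Mann-Whitney and Kruskal-Wallis tests on raw values respond mainly to a shift in location and have little power against a symmetric change in spread. The measure that would register such a gain, deviation from the guideline, is the one primary endpoint with no between-phase test.

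The reverse also holds. A shift that takes cases out of the window is a significant change and meets Endpoint 1.1. The confirmatory result alone therefore cannot say whether feedback brought compressions closer to the guideline. Pauses are not affected, because shorter is better throughout.

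**Working it through.** **Inputs from the protocol.** Phases of 95, 92 and 92 cases ("In total, 95 + 92 + 92 = 279 patients are needed for this project"); local levels 5%/4 = 1.25% for depth, 1.25% for frequency and 5%/2 = 2.5% for pauses; windows 5-6 cm and 100-120/min. The levels sum to 1.25 + 1.25 + 2.5 = 5%, so no alpha is left for Endpoint 1.2.

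**The plan's own figure.** "For the comparisons of compression depth, with these numbers of patients a power of 82.1% is achieved". No effect size or SD is given, so this cannot be reproduced, only solved backwards. Two-sided, with 92 per group, the standardised shift is d = (z₀.₉₉₃₇₅ + z₀.₈₂₁) × √(2/92) = (2.498 + 0.919) × 0.1474 = 0.50. Dividing by √(3/π) = 0.977 for the Mann-Whitney test gives 0.52. The depth comparison is thus powered for a location shift of about half an SD.

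**Share in the window.** For normal case values, share = Φ((upper − mean)/SD) − Φ((lower − mean)/SD). At 110/min with SD 18 this is 2Φ(10/18) − 1 = 42%; with SD 9 it is 2Φ(10/9) − 1 = 73%.

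**Simulation.** All means and SDs are assumptions, because the protocol gives none. Case values are normal, tests are two-sided Mann-Whitney at 1.25%, and groups are 92 vs 92 or 95 vs 92. Distance means max(0, lower − x, x − upper) per case. Ranges are from repeated independent runs.

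| Scenario, mean (SD) | In window | Raw test rejects | Distance test rejects |
|---|---|---|---|
| *Narrowing at the centre* | | | |
| Rate 110 (18) to 110 (9) | 42% to 73% | 1.3-1.7% | over 99% |
| Rate 110 (18) to 110 (12) | 42% to 60% | 1.2-1.4% | 74% |
| Depth 5.5 (1) to 5.5 (0.5) | 38% to 68% | 1.2-1.6% | over 99% |
| *Baseline off centre, moving in and narrowing* | | | |
| Rate 112 (15) to 110 (8) | 49% to 79% | 9% | 99% |
| Rate 115 (15) to 110 (8) | 47% to 79% | 59% | over 99% |
| Rate 120 (15) to 110 (8) | 41% to 79% | over 99% | over 99% |
| Depth 4.5 (1) to 5.0 (0.8) | 24% to 39% | 86-87% | 86% |
| *Shift out of the window* | | | |
| Rate 115 (15) to 123 (15) | 47% to 36% | 84% | 35% |
| Depth 5.8 (1) to 6.3 (1) | 37% to 29% | 78% | 26% |
| *Pure 0.5 SD shift toward the window* | | | |
| Depth 4.5 (1) to 5.0 (1) | 24% to 34% | 79% | 45% |
| Depth 4.8 (1) to 5.3 (1) | 31% to 38% | 78% | 16% |
| Rate 120 (15) to 112.5 (15) | 41% to 49% | 79% | 16% |

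In the three-phase closed test for frequency, with mean 110 and SDs 20, 20 and 10, Phase 1 vs 3 and Phase 2 vs 3 are each rejected in only 0.4-0.5% of runs.

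**The case against.** A reader might infer that a gain in guideline adherence would go unseen. The documents do not support that. Endpoint 1.2 is primary, and a rise from 42% to 73% in the window would show in its description by phase. The gap is that no between-phase test stands behind it.

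A reader might also infer that a shift away from the window would be counted as a success, or as harm to patients. The plan has no success rule. Its hypothesis speaks only of change, and the documents give no outcome data for cases above the window. The planned Hodges-Lehmann estimates would show the direction of a raw shift. They would not show whether it leads toward the window, and they would be near zero under symmetric narrowing.

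Third, no per-case variable is defined, so raw value is a reading and not a statement of the plan. It is the natural reading, because deviation is kept for Endpoint 1.2.

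The strongest objection concerns size and remedy. The near-zero power needs a baseline close to the window centre. With SD 18 to 9, a baseline of 115 moving to 110 already gives the raw test 43-45%, and 118 moving to 110 gives 88-89%. The Introduction says that depth and frequency often missed the guidelines, but not on which side. Under a pure location shift the distance test is clearly weaker. This stands, and it rules out replacing the raw tests.

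**Conclusion.** The point holds in this form: a primary endpoint defined by windows has no between-phase test, and the tests that carry alpha have no direction and little power against symmetric movement into the window. In the centred scenarios tabulated, the raw test rejects in 1.2-1.7% of trials while the in-window share rises by 18 to 31 points (42% to 60%; 42% to 73%). In the two tabulated scenarios that leave the window, it is significant in 78-84% of trials.

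These sizes rest on assumed normal case values, means and SDs, and on reading the tested variable as the raw value. They do not apply to pauses, nor to crews who err mainly on one side. The finding does not invalidate the planned tests. It limits what they can support: change in raw depth or rate, not improvement against the guideline.

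**What to change.** 1. Keep the raw-value tests, and define the per-case summary that they use.
2. For Endpoint 1.2, define the per-case distance outside the window (zero inside) for frequency across all phases and for depth in Phase 2 vs 3. Compare it between phases with the same Mann-Whitney or closed procedure, and give a Hodges-Lehmann estimate with confidence interval. Report the in-window share as well: with 42% and 73% of cases at zero, 0.42 × 0.73 = 31% of pairs tie at zero, which pulls the Hodges-Lehmann estimate toward zero.
3. State its standing. It can be a named supporting test outside the alpha split, or it can take a stated part of the depth and frequency shares with power restated.
4. Claim improved quality only when this measure moves toward the window. A raw-value result alone supports only change.
5. Reconcile the frequency reference, a range of 100-120/min in the Introduction and 100/min under Indicators, because the variable depends on it. A case at 115/min lies inside the first and deviates by (115 − 100)/100 = 15% from the second.

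No new data are needed. A supporting test costs a little analysis, but a gain seen only there is not confirmatory. Sharing alpha costs power. For depth, using the back-solved 3.417 from the working, leaving the raw test 1.0% gives Φ(3.417 − 2.576) = 80%; halving to 0.625% gives Φ(3.417 − 2.734) = 75%, below the plan's 80% floor. For depth, also comment on the stated sensor accuracy of ± 6.25 mm: its span of 2 × 6.25 = 12.5 mm exceeds the 10 mm window.
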